**Figure 2 figure2:**
[figure not shown]
Pilot optimization trial of an engagement intervention for racial and ethnic minority young adults.

### Data Management

A secure REDCap database will be used to enter and manage recruitment, consent, enrollment, and assessment data. Research data will be assigned an identification code and stored separately from participant names and contact information. Only trained members of the research team will have access to the data throughout the study.

### Data Analysis

Acceptability will be based on an average rating above the mid-point of the scale and overall positive thematic qualities in the interview data. Feasibility estimates will be based on recruitment rates and retention rates for assessments and components, component adherence rates, and component fidelity rates. Benchmark criteria for feasibility will be recruitment of 3 participants per month, completed assessment rates of 75%, and components completed by 85% of participants. Quantitative data on feasibility will be summarized with descriptive statistics. Confidence intervals will convey the direction, magnitude, and precision of estimates. Infeasible study elements or elements with low acceptability will be identified and then modified or removed from the protocol before subsequent stages of intervention testing.

For qualitative data, interviews will be transcribed and analyzed to describe and assess the acceptability of the intervention components using procedures for thematic analysis [85] and coding techniques from content analysis [86]. First, analysts will code independently using a priori codes (eg, constructs assessed in quantitative measures) and determine emergent codes based on participants’ responses. Next, analysts will meet regularly to reach consensus on coding and jointly construct common, divergent, and subthemes. These processes will assist analysts to consider and manage how their own perspectives influence or guide the analytic process. Then, verbatim text will be ordered within thematic categories. Finally, data on outcomes that are assessed both qualitatively and quantitatively (eg, acceptability, feasibility, and adherence) will be integrated for side-by-side comparison using matrices and joint displays [87]. We will ensure methodological integrity by using audit trails and transparently documenting all analytic procedures and decisions [88]. Integrated results will be used to inform any future modifications to protocols and procedures for later phases of the intervention adaptation and evaluation process.

To assess treatment engagement outcomes, exploratory analyses will examine the distributions of all variables, identify outliers, and calculate descriptive statistics for each assessment timepoint, and with respect to the 3 components. We will use an intent-to-treat approach for the analysis. Factorial ANOVA using effect coding will be used to estimate the main effects and interactions between factors (ie, components) on the mean change in number of contacts with treatment services and the level of engagement at 3-month follow-up. Each intervention component will be assigned a value of +1 or –1 depending on whether it was included or excluded from the experimental condition (ie, yes or no). In addition, we will explore evidence of effects on mediators at posttest and 3-month outcomes. Analyses will rely on an examination of the overall pattern of changes (eg, strength and change in the intended direction) instead of hypothesis testing. The sample size of 80 is sufficient for the planned analyses and provides 79% power to detect main effects, corresponding to a correlation of 0.6 and a medium effect size (*d*=0.50), given α=.05.

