## Methods

### Pilot Trial Design

This study uses a balanced 2^3^ factorial experiment. Each factor will have 2 factor levels, included (yes) or excluded (no), resulting in 8 experimental conditions that represent all possible combinations of the new candidate components (see Table 1). All participants will receive the Just Do You core component, followed by the candidate components they were assigned to receive, if any. Thus, participants will be randomly assigned to one of 8 experimental conditions and receive Just Do You and 0-3 new components. We will explore preliminary evidence of component effects on the primary outcomes by comparing the mean outcomes across included conditions versus the mean outcomes across excluded conditions. For example, Component A conditions 5-8 will be compared to conditions 1-4. The factorial design does not directly compare each condition or use a traditional control group. Instead, each factor level serves as its own control. Consistent with a convergent parallel mixed methods design [79], semistructured qualitative interviews will be conducted postintervention with participants to provide context and improve our interpretation of quantitative results. A total of 80 participants will be enrolled.

**Table 1 table1:** Experimental conditions in the 23-factorial design.

Experimental condition	Just Do You	Component A	Component B	Component C	Sample size, n
1	Yes^a^	No^b^	No	No	10
2	Yes	No	No	Yes	10
3	Yes	No	Yes	No	10
4	Yes	No	Yes	Yes	10
5	Yes	Yes	No	No	10
6	Yes	Yes	No	Yes	10
7	Yes	Yes	Yes	No	10
8	Yes	Yes	Yes	Yes	10

^a^Yes: component is included.

^b^No: component is excluded.

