### Assessment Procedures

Assessments of engagement will occur at baseline, posttest (after intervention completion), and 3-month follow-up. At each assessment, participants will report on involvement in their treatment, and their perceptions of stigma, benefits, trust and rapport with providers, hopefulness, and the difficulty associated with treatment engagement. In-depth acceptability interviews will be conducted at posttest with 40 participants purposively sampled from each experimental condition. Acceptability interviews will be focused on experiences with intervention components, aspects of implementation, and any factors that promoted or impeded intervention adherence. Each assessment is expected to last for 1 hour.

Screening, consent, and assessment interviews with participants will be administered by the principal investigator or another trained member of the research team and will take place in person at the study site or via encrypted videoconferencing. All staff involved in data collection will be trained on the assessments by the principal investigator, and all research staff will complete training on informed consent, good clinical practices, and all safety and reporting protocols as certified by New York University’s institutional review board (IRB).

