Engagement in treatment will be measured using 8 items from the Client Engagement in Child Protective Services Scale involvement or buy-in subscale [83]. Responses are on a 5-point Likert scale. An example item is “I am not just going through the motions. I’m really involved in working with providers.” The range for the scale is 8 to 40, with higher scores indicating higher levels of engagement. This scale has demonstrated acceptable reliability with the study target population (=.82) [51,83]. Service usage will be measured at a 3-month follow-up by participant medical records. The total number of contacts each participant makes with the treatment program, and the dates for all contacts, starting 1 month before baseline through 3-month follow-up, will be collected to assess change in service use over the study period. Demographic information will be collected at baseline, and targeted mediators and mental health symptoms will be collected by self-report measures at all timepoints. Study measures have been extensively tested by the research team [84] and previous studies with REM populations, young adults, and individuals living with SMI. All have been found to have good psychometric properties. Can be found in Multimedia Appendix 2: Baseline assessment measures for a full list of the study measures collected during the baseline assessment.

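### Engagement is analysed without its baseline score as a covariate, yet the stated 79% power is reached two-sided only with that adjustment

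*Protocol article*

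**What the plan says.** Four statements in the protocol article bear on this.

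- **Model** (Data Analysis): "Factorial ANOVA using effect coding will be used to estimate the main effects and interactions between factors (ie, components) on the mean change", and the sentence continues "in number of contacts with treatment services and the level of engagement at 3-month follow-up". Components are coded +1 or –1. No covariate is named.
- **Measurement** (Assessment Procedures): "Assessments of engagement will occur at baseline, posttest (after intervention completion), and 3-month follow-up". A baseline engagement score is therefore planned for every participant. Mediators are also collected at all timepoints (Measures).
- **Design** (Pilot Trial Design): "A total of 80 participants will be enrolled", in eight conditions of 10. Main effects compare half the sample with the other half: "For example, Component A conditions 5-8 will be compared to conditions 1-4".
- **Power** (Data Analysis): "The sample size of 80 is sufficient for the planned analyses and provides 79% power to detect main effects". The basis given is a correlation of 0.6, d = 0.50 and α = .05. The article does not say which two quantities are correlated or whether the test is one- or two-sided.

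The same section says that the analyses look at patterns of change and do not rest on hypothesis tests.

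**The concern.** The model sentence has two readings for engagement. If the word change governs both outcomes, engagement is a change score. If it governs contacts only, engagement is the unadjusted 3-month level. A change score uses the baseline but gives it a fixed weight of one, and the raw level ignores it. Either way the component contrasts are less precise than with the baseline score as a covariate.

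Two things are at stake. The pilot's estimates are to inform a fully powered optimization trial, so avoidable variance weakens what the pilot is meant to deliver. And the sample size is justified by a power figure in the same paragraph, which should describe the model named there.

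**Working it through.** **Inputs.** N = 80, hence 40 vs 40 for each main effect; d = 0.50; correlation 0.6; α = .05 (Pilot Trial Design, Data Analysis).

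**Assumptions.** The 0.6 correlates baseline with 3-month engagement. The variance is the same at both times. d is in units of the single-time standard deviation, set to 1. The test is two-sided unless marked otherwise.

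**Formulas.** Residual variance is 1 for the 3-month level, 2(1 − r) for change and 1 − r² with baseline as covariate. The noncentrality is d / (SD × √(2/40)) = 0.50 / (SD × 0.2236) = 2.236 / SD. The normal approximation to power is Φ(2.236/SD − 1.96). The t version uses the residual degrees of freedom of the full factorial model: 80 − 8 = 72, or 71 with the covariate.

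**Which model gives the stated 79%?**

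| Analysis of engagement | Residual variance | SD | Noncentrality | Power, normal | Power, t | One-sided power, t | N for 79% (normal) |
|---|---|---|---|---|---|---|---|
| 3-month level | 1.00 | 1.000 | 2.236 | 60.9% | 59.7% | 71.6% | 124 |
| Change | 2(1 − 0.6) = 0.80 | 0.894 | 2.500 | 70.5% | 69.4% | 79.7% | 98 |
| Baseline as covariate | 1 − 0.36 = 0.64 | 0.800 | 2.795 | 79.8% | 78.7% | 86.9% | 80 |

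Among the two-sided analyses only the last row reproduces 79%. A one-sided change-score test comes as close, but the article states no one-sided test. The raw level does not match either way.

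**Size of the loss at r = 0.6.**

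- Change against adjusted: 0.80 / 0.64 = 1.25. Change scores need 25% more participants for the same precision; put the other way, 80 × (1 − 0.64/0.80) = 16 of 80 are given away in information.
- Level against adjusted: 1.00 / 0.64 = 1.56, or 56% more participants.
- Approximate half-width of a 95% CI for a component effect, 1.96 × 0.2236 × SD: 0.44 (level), 0.39 (change) and 0.35 (adjusted), in standard deviations.

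**Sensitivity to r (two-sided t, N = 80).**

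| r | Level | Change | Baseline as covariate |
|---|---|---|---|
| 0.3 | 59.7% | 46.2% | 63.8% |
| 0.5 | 59.7% | 59.7% | 72.1% |
| 0.6 | 59.7% | 69.4% | 78.7% |
| 0.7 | 59.7% | 81.3% | 87.0% |
| 0.8 | 59.7% | 93.7% | 95.7% |

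The ordering between change and adjustment does not depend on r, because 2(1 − r) − (1 − r²) = (1 − r)², which is positive for every r below 1. Below r = 0.5 a change score is worse even than ignoring the baseline; at the stated 0.6 it is better.

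**The case against.** The strongest reply is that the match between 79% and the baseline-adjusted analysis suggests the authors already intend adjustment, and that the article shortened this to ANOVA. That may be so. The paragraph as printed still names one model and reports the power of another, so it needs the correction either way.

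A second reply is that this is an exploratory pilot and that, with randomisation intact, change-score and raw-level contrasts are unbiased. This stands and limits the weight of the point, which concerns efficiency and consistency rather than validity. It does not remove it, because the pilot's product is estimates and the authors chose to justify N by power.

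A reader might go further and infer that the plan is really a complete-case analysis, dropping everyone without a 3-month score, and that 20 of 80 would be lost. The article does not support this:

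- It says "We will use an intent-to-treat approach for the analysis" and gives no rule for missing scores. Such a rule is commonly placed in a full protocol or SAP, and neither is shown.
- The 20 of 80 comes from the 75% assessment-completion figure, which is a feasibility benchmark and not an expected dropout rate.
- The other outcome does not depend on attending the interview: "Service usage will be measured at a 3-month follow-up by participant medical records".

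It would also be too strong to say that the plan discards the baseline altogether. That is true only if engagement is analysed as the raw level.

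**Conclusion.** The point holds as one of efficiency and internal consistency. The named analysis of engagement omits a baseline covariate that is being collected. At the stated inputs this costs about 9 percentage points of two-sided power if engagement is a change score (69.4% against 78.7%) and 19 points if it is the 3-month level (59.7% against 78.7%).

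The sizes rest on reading the 0.6 as the baseline to follow-up correlation, on equal variances, on d in single-time standard deviations, and on a two-sided test. The advantage of adjustment over a change score does not depend on the value of r; the exact match to 79% does.

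No conclusion about missing data follows from the text. Weight: a free improvement.

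**What to change.** 1. Keep the effect-coded factorial model. Analyse 3-month engagement, and each mediator, with its own baseline score as a covariate, and report the component effects with 95% CIs. State in the same sentence that the engagement outcome is the 3-month score.
2. State what the 0.6 correlates and that the test is two-sided; the 79% then stands. If the unadjusted model is kept, restate the power as about 69% (change) or 60% (level).
3. Make sure the baseline score is obtained before the assignment is known. The Study Timeline lists randomization before the baseline assessment on the first day, and the Randomization section says that assignments are unblinded. A baseline answered with knowledge of the assignment could carry a component effect into the covariate, and equally into a change score. If the list is not meant as a sequence, saying so is enough.

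Items 1 and 2 cost a sentence or two and one residual degree of freedom per model. They use data already planned and standard software. Item 3 costs a wording change, or a reordering of first-day procedures if randomization does come first.

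A mixed model that also uses the posttest score is optional. The gain computed here comes from the baseline covariate alone. Posttest follows an intervention lasting 1 to 5 weeks according to condition, so its timing is tied to the assigned components and such a model would have to allow for that.

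### The stated 79% power does not match the covariate-free factorial ANOVA beside it, which gives about 69% on change scores or 60% on the 3-month level

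*Protocol article*

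**What the plan says.** All of the following is in the Methods of the protocol article.

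- **Size and contrast.** Under Pilot Trial Design, "A total of 80 participants will be enrolled", ten in each of eight conditions. Each main effect compares half the sample with the other half; for example, "Component A conditions 5-8 will be compared to conditions 1-4".
- **Model.** Under Data Analysis, a factorial ANOVA with factors coded +1 and –1 will estimate main effects and interactions "on the mean change in number of contacts with treatment services and the level of engagement at 3-month follow-up". No baseline covariate is named.
- **Power.** The same paragraph calls 80 participants sufficient for what is planned and says that this number "provides 79% power to detect main effects, corresponding to a correlation of 0.6 and a medium effect size", with d=0.50 and alpha .05. It does not say which variables the correlation links, whether the test is one-sided or two-sided, or how many of the 80 are expected to have outcome data.
- **Role of testing.** "Analyses will rely on an examination of the overall pattern of changes (eg, strength and change in the intended direction) instead of hypothesis testing".
- **Completion.** The feasibility benchmarks include "completed assessment rates of 75%, and components completed by 85% of participants".
- **Data source.** Under Measures, engagement is a self-report scale, while service contacts are taken from medical records.

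**The concern.** A power figure belongs to a particular model. A correlation of 0.6 plays no part in an ANOVA of follow-up scores alone. In a change-score ANOVA it enters through one variance formula, and in a baseline-adjusted model through another, which gives a smaller variance. The paragraph describes an analysis without adjustment and quotes a figure that looks like the adjusted one.

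At stake is how the component estimates will be read. The pilot is meant to inform a later optimization trial. A reader who believes that a true effect of d=0.50 would be missed about one time in five will give a weak result more weight than one who knows that the described ANOVA would miss it 31% to 40% of the time, even with complete data.

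**Working it through.** **Inputs from the article:** N=80, balanced, so 40 against 40 for each main effect; d=0.50; correlation r=0.6; alpha .05.

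**Inputs assumed here:** a two-sided test (as an ANOVA F test implies); r is the baseline to follow-up correlation; d is in units of the outcome's raw SD; for change scores, baseline and follow-up variances are equal.

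**Formula.** Power comes from the noncentral t distribution for a one-degree-of-freedom contrast, with noncentrality d·√N / (2·√v). Error degrees of freedom are N–8 for the full factorial model and N–9 with one covariate. The residual variance factor v depends on the model:

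- 3-month level: v = 1
- change score: v = 2(1 – 0.6) = 0.80
- baseline-adjusted: v = 1 – 0.6² = 0.64

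**Reproducing the plan's figure.** With adjustment and all 80 analysed, noncentrality = 0.5·√80 / (2·0.8) = 2.795, which gives power of 78.7%. This rounds to the stated 79%.

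**The ANOVA as described, N=80.**

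- Change: 0.5·√80 / (2·0.894) = 2.50, power 69.4%.
- Level: 0.5·√80 / 2 = 2.236, power 59.7%.

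If d=0.50 were meant in SD units of the change score itself, the change analysis would have the level figure, 59.7%.

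**Engagement scale at 75% completion.** 0.75 × 80 = 60, taken as 30 against 30. The noncentralities become 2.421 (adjusted), 2.165 (change) and 1.936 (level).

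**Precision.** The 95% CI half-width for a main effect, in SD units, is t(0.975)·2·√v/√N. With adjustment at N=80 this is 1.994 × 2 × 0.8 / 8.944 = 0.36.

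| Model | Power, N=80 | Power, N=60 | Half-width, N=80 | Half-width, N=60 |
|---|---|---|---|---|
| Baseline-adjusted | 78.7% | 66.1% | 0.36 | 0.41 |
| ANOVA on change | 69.4% | 56.6% | 0.40 | 0.46 |
| ANOVA on 3-month level | 59.7% | 47.6% | 0.45 | 0.52 |

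The N=60 columns concern the engagement scale only.

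**Other routes to 79%.** A one-sided test on change scores at N=80 gives 79.7%. The article states no one-sided test, and on the same basis the level analysis would reach only 71.6%. Reading 0.6 as R² gives 93.7%, which does not fit.

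**The case against.** The strongest reply is that nothing has been miscalculated. The figure of 79% follows from the stated inputs, and a correlation is quoted only if baseline information was used, so the authors probably intended a covariate that a condensed article leaves unnamed. This is plausible, and it makes the repair easy. But the article does name a model, and the power it attaches to that model is not the model's power. Nor does the reply make the figure hold at 75% completion, where the adjusted analysis of engagement has about 66%.

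Several further points stand and limit the finding:

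- **The source of the 79% is inferred.** A reader might take it as established that an ANCOVA was used. The article does not label the correlation, so this cannot be shown.
- **The figures at N=60 do not cover the whole analysis.** A reader might infer that power falls to between 48% and 57% for everything planned. Contacts come from medical records, so missed interviews need not remove anyone from that outcome. For engagement, 57% and 48% are alternatives that depend on whether the word change in the analysis sentence governs both outcomes or only contacts.
- **75% is a benchmark for calling assessments feasible, not a retention forecast.** The article describes active tracking, and how missing data will be handled may be set out elsewhere.
- **Equal variances are an assumption.** If the baseline SD is k times the follow-up SD, the change-score factor is 1 + k² – 2(0.6)k: 0.80 at k=1, and at its lowest, 0.64, at k=0.6. Contacts are counted from one month before baseline to three months after, so k=1 is doubtful for raw counts. Their change-score power could lie above or below 69%, but not above the adjusted figure. For engagement, the same scale is used at each time, so equal variances are the natural assumption.
- **The consequences are bounded.** Effects are described as preliminary, no hypothesis tests are relied on, and the benchmarks concern feasibility and acceptability.

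**Conclusion.** The mismatch is real. On the article's own inputs, the described ANOVA has about 69% power on change or 60% on the 3-month level, which is 9 or 19 percentage points below the stated 79%. Reaching 79% without adjustment would take about 101 participants for change or 125 for level. The stated figure is matched by a baseline-adjusted analysis of all 80. For engagement at the 75% floor, even that analysis has about 66%.

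These results assume a two-sided .05 test, d=0.50 in raw SD units, 0.6 as the baseline to follow-up correlation and, for change scores, equal variances.

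A reader might conclude that the trial is too small or its design unsound. The documents do not support that: this is a preparation-stage pilot that disclaims hypothesis testing. The fault is in one paragraph that describes one analysis and quotes power matching another. Severity is moderate.

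**What to change.** In Data Analysis:

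1. Add the baseline value of each outcome as a covariate in the effect-coded factorial model. For contacts, define the baseline value from the month before baseline.
2. Label the 0.6 as the baseline to follow-up correlation, and state that the test is two-sided.
3. State power as about 79% with complete data and about 66% for engagement at 75% completion.
4. If the unadjusted ANOVA is kept instead, say whether each outcome is analysed as change or as level, and restate power with complete data as about 69% (change, equal variances) or 60% (level).
5. Optionally, since no tests are planned, give the expected 95% CI half-width for a main effect with adjustment: about 0.36 SD at N=80 and 0.41 SD at N=60.

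The cost is the rewording of one paragraph. Baseline engagement and pre-baseline contacts are already collected, so sample size, visits and procedures do not change. The price is a less favourable power statement wherever data are incomplete or the unadjusted ANOVA is kept.
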